### Outcomes measurement

For our primary outcome measure, we will evaluate change in /ɹ/ production accuracy by obtaining perceptual ratings of /ɹ/ production accuracy in the word probe elicited in the pre-treatment evaluation visit and again in a post-treatment assessment visit scheduled within approximately one week of the end of treatment. The word probe consists of 24 words divided evenly across the six /ɹ/ contexts targeted in treatment; to assess generalization, the probe words do not overlap with the word lists targeted in treatment. As in our previous research [15], we will obtain perceptual ratings of /ɹ/ production accuracy from untrained listeners recruited via online crowdsourcing. Raters will be required to report speaking American English since early childhood and must originate from US-based IP addresses. Each word probe recording will be split into word-level productions. These word-level recordings will be pooled across speakers and time points and presented in a randomized order for rating. Raters will see the orthographic representation of each word and will be asked to assign a binary rating (correct/incorrect) to the /ɹ/ sound in each word. Based on the results of our previous methodological research [54, 55], we will collect ratings until at least 9 unique listeners have rated each token. Our primary measure of the accuracy of /ɹ/ production will be the proportion of “correct” ratings out of the total number of ratings, which has been found to correlate strongly with acoustic measures as well as expert listeners’ ratings of /ɹ/ [54, 55].

As a secondary outcome measure, a survey assessing the social-emotional impact of RSSD will be administered to participants and their parents in the initial evaluation and post-treatment assessment [5]. The survey includes 11 items (e.g., “My speech/my child’s speech sounds different from the speech of other children my/their age”; “My speech/my child’s speech has an impact on my/their academic performance”) that are presented with the response options “yes,” “no,” and “sometimes.” Responses will be analyzed using a Generalized Partial Credit Model [56], which combines individual item scores into an overall impact score. Each item is weighted to reflect its stronger or weaker association with the total score.

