In the intention-to-treat analysis, we will impute an outcome for participants who drop out of the study and are lost to follow-up based on data from the individuals who have complete data and are in the same treatment assignment. In the per-protocol analysis, we will attempt to estimate the effect of telehealth versus in-person treatment only for those in the sample who remained in the trial and completed all assessments. Because estimates of this effect can be biased due to systematic differences that arise when focusing on this non-random sample from the trial, we will perform an *adjusted* per-protocol analysis using inverse probability of treatment weighting, following recommendations from recent methodological research [59, 60].

Our primary outcome measure of interest is change in perceptually rated accuracy of /ɹ/ sounds from pre- to post-treatment, with perceptual ratings of pre- and post-treatment probes obtained from blinded listeners as described above. We will compute this change score for all participants and will use a linear model with a fixed effect of group to compute the 95% confidence interval around the difference in change scores between groups. The in-person group will be treated as the reference level, so that a negative value indicates smaller gains when treatment is delivered via telepractice versus in-person. The model will also control for the randomization strata of site and baseline severity group (less stimulable versus more stimulable), as well as baseline accuracy as a continuous predictor. Lastly, we do not plan to include a fixed effect of age because our previous research has not supported such an effect (e.g [61]). However, we will test for a correlation between age and treatment outcomes and if a statistically significant correlation is present, we will include age as a controlled covariate.

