A secondary analysis will report pre- to post-treatment changes on the 11-item survey assessing the social, emotional, and academic consequences of RSSD that will be administered to participants and their parents both before and after the course of treatment. We will model impact score (as defined in [5]) as the outcome variable with fixed effects of time, treatment group, and the time by treatment group interaction, as well as clinician and initial accuracy level. Likelihood ratio tests will be used to assess the significance of fixed effects and interactions in the final model. A significant effect of time would suggest a change in the perceived impact of RSSD over the course of treatment, while a significant interaction between time and treatment group could indicate a difference in the magnitude of the change in perceived impact across treatment conditions.

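### The between-arm test on the impact survey is an unadjusted change-score contrast; using the baseline impact score would gain precision at almost no cost

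*Protocol article*

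**What the plan says.** All references are to the protocol article.

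- **Status and timing.** Outcomes measurement introduces the survey thus: "As a secondary outcome measure, a survey assessing the social-emotional impact of RSSD". It "will be administered to participants and their parents in the initial evaluation and post-treatment assessment", so there are two time points. Assessment process places the impact questionnaire before the eligibility visit, hence before allocation.
- **Model.** In the secondary analysis of the Data analysis plan, the impact score is the outcome, "with fixed effects of time, treatment group, and the time by treatment group interaction, as well as clinician and initial accuracy level".
- **Test.** "Likelihood ratio tests will be used to assess the significance of fixed effects and interactions in the final model".
- **Between-arm reading.** The same paragraph says that "a significant interaction between time and treatment group could indicate a difference in the magnitude of the change in perceived impact across treatment conditions".
- **Primary model, for comparison.** The change in rated accuracy is compared between arms with control for site and stimulability group, "as well as baseline accuracy as a continuous predictor". The primary change score is therefore adjusted for the baseline value of the same measure.

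**The concern.** The baseline impact score enters the secondary model only as one of the two outcome rows. The group main effect lets the arms have different baseline means, although they are randomised after the baseline survey and any true baseline difference is zero by design. The initial accuracy level is a speech measure and does not stand in for baseline impact. Clinician and initial accuracy enter as time-constant main effects, which shift the pre and post scores equally.

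At stake is the precision of the survey comparison between delivery modes in a trial of 76 children. A chance baseline imbalance in impact also passes into the estimate, where a baseline-adjusted analysis would remove it. The primary model already adjusts for its own baseline, and the article gives no reason to treat the survey differently.

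**Working it through.** **Inputs.** From the article: 38 children per arm, 1:1 allocation, one pre and one post survey score. Not in the article: the pre-post correlation rho and the SDs of the impact score. These are assumed below and shown as ranges. The article states no power or precision for the survey, so there is no figure to reproduce; 38 per arm comes from the sample size for the primary outcome.

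**Step 1: what the interaction estimates.** With time coded 0/1 and complete pairs, the time by group coefficient is (post minus pre, telepractice) minus (post minus pre, in-person). Adding the same covariate value to a child's two rows cancels in the difference. One simulated data set with 38 per arm confirmed this:

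| Model | Estimate | SE |
|---|---|---|
| Mixed model with clinician and accuracy | -0.2892 | 0.2162 |
| Mixed model without them | -0.2892 | 0.2162 |
| Plain difference in change scores | -0.2892 | 0.2162 |
| Post score on group and baseline score | -0.2597 | 0.2068 |

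In a second simulated data set with 8 post scores missing, the identity no longer held exactly, but the covariates still did little: -0.021 (SE 0.225) with them, -0.010 (SE 0.224) without.

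**Step 2: precision, equal SDs.** With common SD sigma and n per arm:

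- change contrast: variance = 2(1-rho) x sigma^2 x 2/n
- baseline-adjusted contrast: variance = (1-rho^2) x sigma^2 x 2/n
- ratio adjusted/change = (1+rho)/2, so the share of information lost = (1-rho)/2

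With n = 38 and sigma = 1, the detectable difference (80% power, two-sided 5%) is 2.80 x SE. In each pair below, the change contrast comes first and the adjusted contrast second.

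| rho | Loss | 76 x (1+rho)/2 | SE | Detectable difference (SD) | Power for an assumed 0.5 SD |
|---|---|---|---|---|---|
| 0.3 | 35% | 49.4 | 0.271 / 0.219 | 0.76 / 0.61 | 45% / 63% |
| 0.5 | 25% | 57.0 | 0.229 / 0.199 | 0.64 / 0.56 | 59% / 71% |
| 0.7 | 15% | 64.6 | 0.178 / 0.164 | 0.50 / 0.46 | 80% / 86% |
| 0.9 | 5% | 72.2 | 0.103 / 0.100 | 0.29 / 0.28 | above 99% / above 99% |

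A simulation of 4000 runs gave change/adjusted variance ratios of 1.54, 1.31 and 1.18 at rho 0.3, 0.5 and 0.7. The formula 2/(1+rho) gives 1.54, 1.33 and 1.18.

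**Step 3: unequal SDs.** Let k be the post/pre SD ratio, with pre SD 1. The change variance is proportional to 1 + k^2 - 2 x rho x k, and the adjusted variance to k^2 x (1-rho^2).

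- k = 1.2, rho = 0.7: 0.76 against 0.734, loss about 3%
- k = 1.2, rho = 0.5: 1.24 against 1.08, loss about 13%
- k = 0.8, rho = 0.5: 0.84 against 0.48, loss about 43%

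**Step 4: chance imbalance.** With equal SDs, a baseline difference d shifts the change contrast by (1-rho) x d in size. With 38 per arm, d has SD sqrt(2/38) = 0.229 SD units. At rho 0.5, an imbalance of that size moves the estimate by 0.5 x 0.229 = 0.11 SD.

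**The case against.** The strongest reply is that this is a standard and valid pre/post model. Under randomisation the interaction is unbiased, and choosing a baseline-adjusted analysis instead could be called preference. Little rests on the contrast: the paragraph sets out first to report change over time, the interaction is interpreted cautiously, and the survey has no margin, power claim or decision rule. All of this stands, and it limits the point to efficiency. It does not remove the point, because the model and the contrast are stated choices, the baseline score is already collected, and the primary model already adjusts in this way.

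A reader might infer more than the article supports:

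- **That the survey result would be biased or invalid.** Over randomisation it is not. The imbalance in Step 4 is part of its sampling variance.
- **That the non-inferiority conclusion is affected.** It depends wholly on the primary model.
- **That a fixed share, such as 15-35%, is lost.** That range needs rho between 0.3 and 0.7 and equal SDs, and the article gives neither.
- **That pairing within child is ignored because no participant term is named.** A condensed article may leave random effects to the full plan. The point here holds with a participant random effect in the model.
- **That clinician and accuracy were meant to adjust the interaction and fail to.** The article only lists them as fixed effects and does not say what they are for.

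Attrition is expected, so exact invariance to the covariates will not hold in practice. In the check with missing post scores, though, the shift was small.

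**Conclusion.** The point holds as a nearly free improvement to a secondary analysis. The planned between-arm survey test is the unadjusted difference in mean change and is in general less precise than a comparison that uses the baseline impact score. Its size cannot be fixed from the article. With equal SDs the loss runs from about a third at a low correlation to about a twentieth at 0.9. With unequal SDs it can be near zero or above 40%. Adjustment does not lose large-sample precision in any of these cases. That the clinician and accuracy main effects leave the contrast unchanged is exact for complete pairs and approximate otherwise.

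**What to change.** Keep the pre/post mixed model with a participant random effect, but give both arms a common baseline mean: drop the group main effect and keep time and time by group. Let the variance differ between the two time points, so that the gain does not depend on equal SDs. Let the baseline covariates interact with time: initial accuracy or stimulability group, and either site or clinician. If each clinician works at only one site, entering both as fixed effects would alias them. This version keeps the time effect that the plan wants to report.

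For the between-arm contrast alone, an alternative is to model the post-treatment impact score on group, baseline impact score and the randomisation strata, and to report the adjusted difference with its 95% CI. That model gives no time effect, which would need a separate analysis.

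The cost is a wording change and a few degrees of freedom, with no new data. The covariate list should stay short. In a simulation at rho 0.7 with four clinicians, adjusting for baseline alone gave a variance of 0.88 of the change contrast's; adding clinician and accuracy raised it to 0.91.

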## Discussion

### Potential significance

When the proposed data collection is complete, we will have measured changes in /ɹ/ production accuracy, as well as patient-reported outcomes, in children randomized to receive a standard course of biofeedback treatment either via telepractice or in-person. This study will fill a need for high-quality evidence to guide clinical practice as the SLP field shifts toward greater use of telepractice [18, 19]. Developing engaging, evidence-based materials for online use has been identified as one of the most significant challenges for telepractice service delivery [62]. This study aims to scientifically validate an interactive tool for biofeedback treatment via telepractice that is widely available to practicing SLPs. Evidence for the efficacy of biofeedback in the telepractice context could be particularly valuable because children who would otherwise be unable to access biofeedback services may gain access through remote providers.

### Potential limitations

It is important to acknowledge the limitations of the present study. Non-inferiority trials are known to pose a number of challenges for causal inference. First, the definition of the “minimum clinically important difference” is inherently subjective, and there is a lack of agreement in the literature on what criteria to use when setting the parameter Δ (e.g., half of the MCID [27] or 75% of the MCID [28]). We set Δ to 10.4% points based on our reanalysis of previously completed studies, but we acknowledge that other researchers could review the same data and draw a different conclusion about the minimum bound for a clinically meaningful difference between groups.

A second limitation of the non-inferiority design is the potential for non-adherence to the proposed treatment package to influence the conclusions of the study. In our research, the most common form of non-adherence is early study termination. If the types of study participants who terminate early in one condition are different from those that terminate early in the other, the intention-to-treat analysis might provide an overly optimistic assessment regarding non-inferiority. However, if these differences are explainable by our observed covariates, our adjusted per-protocol estimate could help remedy this situation. In accordance with recommendations for non-inferiority studies, we intend to report the results of the VISIT trial using both intention-to-treat and per-protocol analyses. For a strong conclusion of non-inferiority, both methods must show no difference between the treatment conditions exceeding the margin Δ. The US Food and Drug Administration recommends “close examination” of results where a discrepancy is observed between the intention-to-treat and per-protocol analyses. For example, consider a hypothetical scenario where the true effect size of treatment is smaller in the online condition than the in-person condition, but attrition is higher in the in-person condition, which could arise if participants find it more challenging to comply with the prescribed treatment schedule when visits are in-person. This could manifest as a difference in outcomes between the intention-to-treat analysis and the per-protocol analysis, with the latter showing a difference between treatment conditions and the former showing none. While such a finding would not support a strong conclusion of non-inferiority, it could still provide valuable information about real-world strengths and limitations of different service delivery methods. The inclusion of such results in the evidence base could help clinicians and clients make an informed decision based on their own personal values and needs.

An additional limitation of the present study is the possibility that either clinicians or participants/parents could carry their own preference for one service delivery context over another. While we have made every effort to maintain equipoise in our study planning discussions and in how we represent the study to potential participants, there is no way to completely eliminate individual bias. However, we consider information about participant and family preferences to be inherently valuable. We will administer surveys to collect this information in a systematic way and will take these expressed preferences into consideration alongside evidence of efficacy in our interpretation of outcomes.

Finally, some limitations of the generalizability of the findings of this study should be acknowledged. Our primary outcome measure assesses /ɹ/ production accuracy at the word level, rather than at higher levels (sentence or conversation) that might be more representative of learners’ ability in naturalistic communicative situations. The primary outcome measure also evaluates accuracy within a few days of the final treatment session, rather than evaluating the maintenance of gains on a longer time level. However, we do plan to measure participants’ performance six weeks after the end of treatment as part of a separate but related study (not described here) investigating the maintenance of gains made through biofeedback intervention. Lastly, the conditions of treatment delivery in the present study – up to two hours of individual treatment per week – are not reflective of real-world practice patterns for the great majority of SLPs. In the school setting, for instance, SLPs are likely to see children with speech goals in group rather than individual sessions, and the number of minutes of treatment per week is likely to be lower. Our goal in the present study is to measure the efficacy of treatment in a somewhat idealized context; in future research, we hope to shift our focus to the effectiveness of treatment delivered under more realistic conditions.

## Data Availability

https://osf.io/wysv9/.

## Abbreviations

RSSD: Residual speech sound disorder
SLP: Speech-language pathologist
KR: Knowledge of results (feedback)
KP: Knowledge of performance (feedback)
LPC: Linear predictive coding (spectrum)
MR: Magnetic resonance (imaging)
CAS: Childhood apraxia of speech
CELF-5: Clinical Evaluation of Language Fundamentals - Fifth Edition
GFTA-3: Goldman -Fristoe Test of Articulation - Third Edition
OBS: Open Broadcaster Software
FLAC: Free lossless audio codec
MCID: Minimum clinically important difference
staRt: Speech therapist’s app for “R” treatment
BRANY: Biomedical Research Association of New York
Hz: Hertz
kHz: Kilohertz
PC: Personal computer
